## Abstract

**Background:**

Placebo-controlled surgical trials are recognised as the gold standard way to test the efficacy of a surgical procedure. Despite a rise in arthroscopic subacromial decompression (ASD) surgeries for the treatment of shoulder pain, only two placebo-controlled surgical trials have been conducted. These trials encountered significant recruitment challenges, threatening the external validity of findings. Difficulties with recruitment are common in clinical trials and likely to be amplified in placebo-controlled surgical trials. This mixed method feasibility trial aims to address the following questions: (i) Feasibility: What proportion of patients who have consented to undergo ASD report that they would be willing to enrol in a placebo-controlled trial for this procedure? (ii) Optimisation: Can patients’ willingness to enrol in, or understanding of, such a trial be improved by supplementing written consent materials with a brief visual animation that outlines the details of the trial? And (iii) exploration: What factors influence patients stated willingness to enrol in such a trial, and how do they believe the recruitment process could be improved?

**Methods:**

This study aims to recruit 80 patients on the waiting list for ASD. Participants will be randomised (1:1) to either view a brief video animation explaining the hypothetical placebo-controlled trial in addition to written information or to written information only. Participants in both groups will be required to state if they would be willing to opt-in to the hypothetical ASD trial after immediately being presented with the consent material and again 1 week after completion of the consent process. Patients in both groups will also be required to complete a measure of trial literacy. Twenty participants will be purposively sampled to take part in an embedded qualitative study exploring understanding of trial concepts and factors contributing to willingness to opt-in.

**Discussion:**

This feasibility study will provide evidence for optimising participant recruitment into a placebo-controlled trial of ASD by consenting patients using animated trial information in addition to written information. This pilot and feasibility data may also be relevant to placebo-controlled surgical trials more broadly, which are characterised by recruitment challenges.

**Trial registration:**

ANZCTR, ACTRN12620001132932, date October 30, 2020

**Supplementary Information:**

The online version contains supplementary material available at 10.1186/s40814-021-00782-7.

## Background

Placebo-controlled surgical trials are considered the gold standard for testing the efficacy of surgical procedures [1]. Although important disagreements about how best to define the concept of a surgical placebo have yet to be resolved [2], it is widely accepted that these control interventions should at the very least aim to mimic the standard surgery so patients are unaware of which arm of the trial they are enrolled in, and exclude any parts of the procedure that are thought to have a therapeutic effect [1, 3]. By comparing the outcomes of patients who have been randomised to receive a placebo procedure to those who have had the standard surgery, trialists can assess the effectiveness of the standard therapy over and above non-specific and placebo effects. In orthopaedics, placebo-controlled surgical trials have helped change the practice landscape. The most well-known example of such changes relates to knee arthroscopy. Four placebo-controlled surgical trials have shown that knee arthroscopic lavage and debridement offer no benefit over and above the placebo effect [4–7]. Clinical guidelines now recommend against this procedure, suggesting that billions of dollars previously spent on these procedures every year should be put to better use [8, 9].

In light of these findings, placebo-controlled trials of other arthroscopic procedures are now garnering increased attention. One area of recent interest has been arthroscopic subacromial decompression (ASD) surgery for the treatment of shoulder pain [10, 11]. The two placebo-controlled trials of ASD conducted to date faced significant delays with recruitment. Comparing data from their clinical trial registry entries with their published results demonstrates that both trials ultimately required substantially more time to recruit than they had initially scheduled for both recruitment and patient follow-up. In both of these trials, the actual time to achieve target recruitment exceeded the target trial duration, with both trials requiring more than double the number of additional recruitment sites to achieve this. Difficulties with recruitment is common in clinical trials, with only one third meeting their target sample size [12]. This not only represents a significant waste of funds; it also raises ethical concerns. Patients who have enrolled in an underpowered or abandoned trial may have been exposed to unnecessary risk without contributing to the generation of new and meaningful medical knowledge [13]. The problem of low recruitment is likely to be amplified in placebo-controlled surgical trials. Patients may be reluctant to undergo an invasive placebo procedure without the expectation of some form of therapeutic benefit. Difficulties understanding concepts such as equipoise, placebo effects, randomisation, and blinding may also leave many patients confused and unwilling to participate in a placebo-controlled surgical trial [14].

Amongst the most commonly reported reasons for poor recruitment to surgical RCTs include difficulty understanding and a negative attitude towards trial concepts, and a preference for one form of treatment [14]. In line with these findings, Isaksson et al. [15] identified the two most important factors for enhancing recruitment in a RCT as (1) the research question needs to be considered important and (2) a simple procedure for providing information and gaining consent. One such strategy identified to help improve informed consent and therefore enhance recruitment includes the use of video animation. There is some evidence of the positive impact of video animation on enhancing patients’ understandability of research and attitude about participation in clinical research [16–19]. While two studies have shown that the use of educational videos do not, on their own, have a substantial impact on patients’ willingness to enrol in cancer-related trials [16, 17], the use of animated consent materials for placebo-controlled surgical trials has not been explored.

The challenges faced by previous trials highlight the pressing need to carefully evaluate the feasibility of placebo-controlled surgical trials early in the trial planning process. During the process of establishing the feasibility of such trials, there is also an imperative to assess the impact of concrete interventions that aim to optimise the trial’s likelihood of success. Moreover, there is a need to explore new avenues to optimise the feasibility of planned trials by engaging with key stakeholders. Taken together, these considerations provide a framework for this mixed-methods feasibility study, which aims to address the following questions.
*Feasibility*. What proportion of patients who have consented to undergo ASD report that they would be willing to enrol in a placebo-controlled trial for this procedure?*Optimisation*. Can patients’ willingness to enrol in, or understanding of, such a trial be improved by supplementing written consent materials with a brief visual animation that outlines the details of the trial?*Exploration*. What factors influence patients stated willingness to enrol in such a trial, and how do they believe the recruitment process could be improved?

## Methods/design

### Trial design

To answer each of the research question outlined above, we will undertake a two-arm, randomised feasibility trial with an embedded qualitative component. The quantitative component of this study has been designed to test the hypothesis that supplementing written consent materials with a brief animated video leads to patients being more likely to consent to a trial comparing a placebo-control to ASD. This study will be carried out at St. Vincent’s Public Hospital Melbourne (SVHM) in Australia and will involve the recruitment of participant from both SVHM and from associated SVHM surgeon’s private clinic lists. The study strategy is registered, constructed, and presented according to the recommendations of the SPIRIT [20] and CONSORT extension for pilot and feasibility trials guidelines [21] (see Additional File 1). Ethical approval has been obtained from St. Vincent’s Hospital Melbourne Human Research Ethics Committee (reference number LRR 069/20, date 23 September, 2020). The trial has been registered with Australian New Zealand Clinical Trials Registry (ACTRN12620001132932, date October 30, 2020).

### Participants

Given orthopaedic surgeons in Australia often work in both public and private settings, participants will be identified from the SVHM orthopaedic public clinic lists and from the private rooms of surgeons who conduct surgery at SVHM. Individuals will be consented to participate in the feasibility study via telephone call with a member of the research team. After approximately 1 week, individuals will be contacted again to confirm participation. Patient-specific health and sociodemographic information will be collected to test for relevant differences between patients in each arm of the trial. A set of three questions will be used to assess functional health literacy (adapted from Ghanouni et al. [22]). These questions will specifically measure participants stated ease of understanding of medical statistics and written information, and an objective numeracy measure. In addition, we will measure trial literacy using the Therapeutic Misconception Scale. A measure of the participants’ general health status, including both physical and mental health, will be derived using the VR12 [23]. Symptom severity will be derived from a validated questionnaire (Oxford Shoulder Score [24]).

A subset of purposively sampled participants that represent a range of ages and gender from each study arm (approximately 20 in total) will be invited to participate in a phone audio-recorded qualitative interview. After the collection of all other outcome data, these participants will be asked to review the consent material (either written or video animation) while verbalising their immediate responses to these materials, using a ‘think aloud’ technique [25]. This will provide insight into how participants understand key concepts about the study design such as randomisation, blinding, and the use of placebo controls [26].

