### Outcomes

#### Primary outcome

The primary outcome is the proportion of participants who state that they would be willing to opt into the hypothetical ASD trial after being presented with the relevant consent materials. As is common with complex trials, participants will be encouraged to review and discuss trial information before, during, and after consenting to participate. Therefore, outcome measures will be collected immediately after participating in the informed consent process (*t*_2_) and at a second time-point 1 week after completion of the consent process (*t*_3_).

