### Sample size justification

As a feasibility study, no formal power calculation is needed [28]. Based on recommendations for sample sizes for feasibility studies [29], we have set a maximum target of 40 participants per arm (approximately 80 in total) to ensure adequate representation of males and females from both public and private hospital settings. In qualitative research, data collection and data analysis are conducted in parallel and the sample size is determined by thematic saturation. As such, an a priori sample size calculation is not appropriate as it is not possible to know in advance when saturation will be reached. Previous qualitative studies embedded in orthopaedic trials have reached saturation at 12 [30] to 18 participants [31]. Therefore, the sample size of 80 participants will also be sufficient to enable the embedded qualitative evaluation.

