### Randomisation and masking

To minimise bias, participants will be informed that the study aim is to explore patient understanding of informed consent procedures for a placebo surgery trial, but specific details about differences between these consent procedures will not be provided. Participants will only receive information on the mock trial arm they are randomised to and will receive no information about the comparator arm for the duration of the study. After being consented to this feasibility trial, participants will be randomly assigned in a ratio of 1:1 to either arm of the trial. Block randomisation will be performed by an investigator not involved in participant recruitment using computer-generated random assignment sequence prepared in blocks of four and stored in a password-protected file. A research assistant independent of recruitment and data collection will be responsible for participant management. The research associate (who will be responsible for patient consent) will be blinded to group allocation at the time of consent. In addition, outcome ascertainment will be blinded. Upon completion of the study, a biostatistician blinded to group allocation will analyse outcome data.

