### Analysis

#### Quantitative analysis

Categorical variables will be analysed using chi-square tests. For continuous variables, we will employ (parametric) *t* tests and (non-parametric) Mann-Whitney tests for symmetrically and asymmetrically distributed data, respectively. Analyses will be conducted on an intention-to-treat basis by a blinded statistician using Stata, version 14.0 (StataCorp, College Station, Texas).

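### Baseline data are to be tested between randomised arms, while the named outcome tests are unadjusted; describe baseline instead and pre-specify one or two covariates

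*Protocol article*

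**What the plan says.** **Baseline data.** Under Participants, the article says: "Patient-specific health and sociodemographic information will be collected to test for relevant differences between patients in each arm of the trial". The measures are three health-literacy and numeracy questions, the VR-12, the Oxford Shoulder Score and sociodemographic items. Timelines and Table 1 place them before allocation.

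**Tests.** The Quantitative analysis section states "Categorical variables will be analysed using chi-square tests". It continues: "For continuous variables, we will employ (parametric) *t* tests and (non-parametric) Mann-Whitney tests", chosen by whether the distribution is symmetric. The wording is general, so it covers baseline variables and outcomes alike. No covariate or regression model is named.

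**Allocation.** Under Randomisation and masking, "participants will be randomly assigned in a ratio of 1:1 to either arm of the trial". The list is computer-generated in blocks of four by someone outside recruitment, and the person taking consent does not know the allocation. No stratification factor is named.

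**What is compared.** Trial design sets out the hypothesis that "supplementing written consent materials with a brief animated video leads to patients being more likely to consent". The primary outcome is binary: "The primary outcome is the proportion of participants who state that they would be willing to opt into the hypothetical ASD trial". The secondary outcome is the Therapeutic Misconception Scale. The target is at most 40 per arm, set without a power calculation.

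**The concern.** A significance test between arms asks whether an observed difference could be due to chance. For a variable measured before a properly run random allocation, it is due to chance by construction. The p-value therefore says nothing about whether an imbalance matters for the outcome comparison. That depends on the size of the imbalance and on how strongly the variable predicts the outcome.

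A reader of the results could be misled in two ways. A chance p-value below 0.05 may cast doubt on a sound randomisation or prompt adjustment chosen after seeing the data. A non-significant difference in a strongly prognostic variable may be taken as reassurance.

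The baseline measures could do more useful work. The Background names difficulty in understanding trial concepts as a reason for refusal, so on the article's own reasoning health literacy may predict both willingness and therapeutic misconception. Adjusting for such a variable can sharpen the comparison. The article's Discussion expects that comparison to provide usable evidence on the relative effect of the video, although the study is labelled a feasibility trial.

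**Working it through.** **Inputs from the article.** 40 per arm, 2 × 40 = 80 in total, which agrees with the stated total. Allocation is 1:1. No significance level, effect size, opt-in rate or prognostic strength is given, so there is no power figure to reproduce.

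**Assumptions.** Two-sided 5% level; 6 to 12 independent baseline variables; a range of prognostic strengths.

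**1. False alarms.** The chance of at least one p < 0.05 among k independent tests is 1 − 0.95^k.
- k = 6: 1 − 0.735 = 0.27
- k = 9: 1 − 0.630 = 0.37
- k = 12: 1 − 0.540 = 0.46

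**2. Missed imbalance.** The standard error of a standardised mean difference is √(2/40) = 0.224, so p < 0.05 needs a difference of 1.96 × 0.224 = 0.44.
- Power to flag a true difference of 0.2, 0.3 or 0.4 is 14%, 27% or 43%.
- Randomisation alone gives an absolute difference above 0.3 in 18% of trials for each variable: 0.3/0.224 = 1.34, and 2 × (1 − Φ(1.34)) = 0.18. None of those between 0.3 and 0.44 would be flagged.

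**3. What an unflagged imbalance can do.** Suppose the baseline difference has z = 1.5 (not significant) and the variable correlates ρ with the outcome. Given that imbalance, the unadjusted test statistic under no effect has mean 1.5ρ and variance 1 − ρ². Its conditional type I error is 6%, 8% or 10% for ρ = 0.3, 0.5 or 0.7. Averaged over all randomisations it stays at 5%.

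**4. Gain from adjustment, Therapeutic Misconception Scale.** The effective sample size is N/(1 − R²).
- R² = 0.10: 80/0.90 = 89
- R² = 0.25: 80/0.75 = 107

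**5. Gain from adjustment, opt-in.** Simulation with N = 80, 2,000 runs per setting, one standardised covariate and an assumed treatment log-odds ratio of 1.2, which is about 35% against 65% when the covariate has no effect. The chi-square test (no continuity correction) is compared with a likelihood-ratio test from adjusted logistic regression.

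| Covariate log-odds per SD | Power, chi-square | Power, adjusted |
|---|---|---|
| 0 | 0.78 | 0.77 |
| 0.5 | 0.72 | 0.73 |
| 1.0 | 0.63 | 0.70 |
| 1.5 | 0.51 | 0.63 |

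With no treatment effect, both methods rejected in about 5% to 6% of runs. The simulation standard error near a power of 0.7 is √(0.7 × 0.3/2000) = 0.01, so a one-point difference should not be read as a gain or a loss.

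**The case against.** The strongest reply is that the named tests are correct. Under 1:1 randomisation, chi-square, t and Mann-Whitney tests are valid, the simulation confirms it, and this is a feasibility study that makes no power claim. The article does not exclude adjusted models, and an analysis plan that is not shown could add them. All of this stands. A reader might infer that the unadjusted analysis is biased or invalid; the article does not support that. The inflation to 6–10% is conditional on a chosen imbalance and correlation.

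A reader might also infer that the baseline data are wasted. They are not: Table 1 lists the measures as participant characteristics, and age and gender guide the interview sample.

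Nor does anything in the article make the outcome analysis depend on a baseline p-value. The misuse described above is a risk, not a stated rule. The article does not use the word p-value, and a descriptive check is a possible reading. Beside an analysis section that consists of significance tests, though, testing is the natural one.

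The figures also have limits:
- The count of 6 to 12 variables is assumed. The named measures are probably correlated, so the false-alarm range is indicative.
- The 89 to 107 figure concerns only the secondary outcome, under an assumed R². Table 1 schedules that scale only at *t*2 and *t*3, so its own baseline value is not available as a covariate.
- For opt-in, gains of 7 to 12 points appear only with a strong covariate.

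What the reply does not remove is the stated purpose of the baseline data. Adding covariates in an analysis plan would leave that sentence as it is.

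**Conclusion.** The point holds in a limited form. The stated purpose of testing baseline differences between randomised arms is a poor choice and should be changed. Under the stated assumptions it carries a 27% to 46% chance of at least one false difference, and it cannot reliably flag standardised differences below about 0.44.

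The unadjusted outcome tests are valid on average. Their possible cost is precision, and its size cannot be fixed from the article because prognostic strength is not given. The range is about none to 12 power points for opt-in, at an assumed log-odds ratio of 1.2, and the equivalent of 9 to 27 extra patients for the Therapeutic Misconception Scale at an assumed R² of 0.10 to 0.25. This is an inexpensive improvement to make, not a flaw that undermines the trial.

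**What to change.** **Baseline.** Replace the sentence under Participants with a statement that baseline characteristics will be summarised by arm, without p-values, to describe the sample and show the size of any imbalance.

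**Outcomes.** Before unblinding, name one or two covariates that are known before allocation and expected to be prognostic, for example health literacy and public or private setting. Report:
- the adjusted risk difference for opt-in, from logistic regression with standardisation;
- the adjusted mean difference in the Therapeutic Misconception Scale, from linear regression.

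Give each with a confidence interval, beside the planned unadjusted comparison.

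**Cost.** A sentence of rewording and two standard models in the software already named, with no new data.

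**Downside.** Few opt-in events would limit the logistic model. If 20% to 30% opt in (an assumption), 80 patients give 16 to 24 events. With arm plus two covariates that is 16/3 ≈ 5 to 24/3 = 8 events per coefficient; with arm plus one covariate it is 16/2 = 8 to 24/2 = 12. The simulation was centred on 50% opt-in, about 40 events, and so is kinder than this. The covariate set should therefore be very small, and the unadjusted result should be kept alongside.

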### Inclusion criteria

Patients will be considered for inclusion if they are the following:
Are aged 18 years or olderHave consented for arthroscopic subacromial decompression (ASD) with one of the orthopaedic surgeons from St. Vincent’s Hospital Melbourne (SVHM) or have consented to surgery at the private rooms of a surgeon who conducts surgery at SVHMUnderstand written and audio-visual instructions in English

### Exclusion criteria

Patients will be excluded from consideration if they are the following:
Undergoing revision surgeryUnable to provide informed consent due to mental incompetence (e.g., intellectual disability, dementia)Non-English-speaking

### Planned interventions

Participants will be presented with the informed consent materials for the arm to which they are randomised. Block randomisation will be used to allocate even numbers of participants to each arm. The consent materials used during the intervention will be presented to each participant individually, by one of the research team members.

